### Analysis population

#### Safety analysis population.

All subjects who have received at least one dose of the study drug (filgotinib) will be included in the safety analysis population.

#### Full analysis set (FAS).

All subjects who have received the study drug (filgotinib) and have valid efficacy data with at least one measurable point will be included in the FAS, which will be used for efficacy analysis.

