### Allocation and blinding

A minimization method is used with history of bDMARDs use (yes/no) and anti-cyclic citrullinated peptide antibody status (positive/negative). Eligible patients will be randomly assigned electronically by a central system in a 1:1 ratio to either the combination therapy group (Add-on group) or the group switched to filgotinib monotherapy (Switch group). This is an open-label trial with no blinding implemented.

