#### Secondary endpoints.

1) Remission achievement rate

The rate of achieving remission at each time point based on DAS28-CRP, Simplified Disease Activity Index (SDAI), Clinical Disease Activity Index (CDAI), and Boolean criteria will be analyzed. The denominator for the proportion will be the number of full analysis set (FAS) in each group, and subjects who discontinue early will be considered as non-achievers. The definition of remission is as follows: DAS28-CRP < 2.6, SDAI ≤3.3, CDAI ≤2.8, Boolean criteria with ≤1 for all of the following items: tender joint count, swollen joint count, patient visual analog scale (VAS), and CRP.

2) Low disease activity achievement rate

The rate of achieving low disease activity at each time point based on DAS28-CRP, SDAI, and CDAI will be analyzed. The denominator for the proportion will be the number of FAS in each group, and subjects who discontinue early will be considered as non-achievers. The definition of achieving low disease activity is as follows: DAS28-CRP ≤ 3.2, SDAI≤11, and CDAI≤10.

3) Change from baseline in DAS28-CRP, SDAI, and CDAI

Change from baseline in DAS28-CRP, SDAI, and CDAI at each time point will be analyzed.

4) ACR20/50/70 and ACR-N achievement rates

Achievement rates of ACR20, ACR50, and ACR70, as well as ACR-N at each time point, will be analyzed. For ACR20, ACR50, and ACR70, the denominator for the proportion will be the number of FAS in each group, and subjects who discontinue early will be considered as non-achievers.

5) Functional remission achievement rate

The rate of achieving functional remission in Health Assessment Questionnaire (HAQ) at each time point will be analyzed. The denominator for the proportion will be the number of FAS in each group, and subjects who discontinue early will be considered as non-achievers. Functional remission is defined as HAQ ≤ 0.5.

6) Structural remission achievement rate

The rate of achieving structural remission in modified Total Sharp Score (mTSS) at week 24 and week 48 will be analyzed. The denominator for the proportion will be the number of FAS in each group, and subjects who discontinue early will be considered as non-achievers. Structural remission at both week 24 and week 48 is defined as an mTSS progression of ≤0.5.

7) Clinical relevant radiographic progression (CRRP, ΔmTSS ≥3) and rapid radiographic progression (RRP, ΔmTSS ≥5) rates

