### Statistical methods

For the primary endpoint, the change in DAS28-CRP from baseline will be analyzed using a Mixed Effects Model for Repeated Measures (MMRM). This method considers the baseline measurement as a covariate and incorporates group, time point, and the interaction between time point and group as fixed effects. It also reflects the variance-covariance structure of repeated measurements within each patient. Using this model, the least squares mean difference between groups at week 24 and its 90% confidence interval will be calculated. Non-inferiority will be confirmed if the upper limit of this 90% confidence interval is less than 0.6.

For the secondary endpoints, the proportion of patients meeting each endpoint and the corresponding 95% confidence intervals will be calculated. For the change from baseline in each endpoint, summary statistics (number of patients, mean, standard deviation, minimum, median, and maximum) will be presented. Additionally, the change from baseline will be analyzed using the same MMRM approach as for the primary endpoint, estimating the least squares mean and its 95% confidence interval at each time point.

As a sensitivity analysis, stratification will be performed based on stratification variables (history of bDMARD use and anti-CCP antibody positivity/negativity), and summary statistics will be calculated for baseline values, measurements at each time point, and changes from baseline by treatment group and treatment period, with intergroup comparisons conducted using t-tests.

Additionally, as a supplementary analysis, in the PPS population, intergroup comparisons of changes from baseline will be conducted using MMRM, and summary statistics will be calculated with intergroup comparisons performed using t-tests. Furthermore, in the PPS population, stratification based on the aforementioned stratification variables will be conducted, and summary statistics will be calculated for baseline values, measurements at each time point, and changes from baseline by treatment group and treatment period, with intergroup comparisons conducted using t-tests.

For the cumulative values of CRP and MMP-3, the AUC for each participant will be calculated, and summary statistics (number of patients, mean, standard deviation, minimum, median, and maximum) for each group will be presented.

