For the safety analysis, treatment-emergent adverse events (TEAEs) observed during the period from the start of the study treatment to the end of the observation period will be summarized. Adverse events that cannot be ruled out as being causally related to the study treatment will be classified as adverse drug reactions. For each group, the number and percentage of cases of TEAEs and adverse drug reactions will be summarized by system organ class and preferred term. Additionally, a summary by severity level will also be provided.

Missing data at each time point will not be imputed. For patients who discontinue the study, only the data obtained up to the point of discontinuation will be used for analysis. Additionally, when analyzing the proportion of patients who achieve the endpoint, cases with missing data at each time point, including those who discontinued the study, will be considered as non-responders and included in the denominator.

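### The full analysis set omits randomised patients who never start filgotinib, and no all-randomised efficacy analysis is described in this open-label trial

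*Protocol article*

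**What the plan says.** The FAS section of the protocol article includes subjects who "have received the study drug (filgotinib) and have valid efficacy data with at least one measurable point will be included in the FAS", and makes that set the basis of the efficacy analysis. It does not say whether the measurable point must come after baseline. The per protocol set is a subset of the FAS.

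Under Secondary endpoints, the rule for the remission, low disease activity, ACR20/50/70, functional and structural remission rates is: "The denominator for the proportion will be the number of FAS in each group, and subjects who discontinue early will be considered as non-achievers". The rates of clinically relevant and rapid radiographic progression (CRRP and RRP) also use the FAS as denominator.

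Statistical methods adds that, for proportions, "cases with missing data at each time point, including those who discontinued the study, will be considered as non-responders and included in the denominator". For other analyses of patients who discontinue, "only the data obtained up to the point of discontinuation will be used for analysis". The primary endpoint is the week-24 change in DAS28-CRP, analysed with a mixed model for repeated measures (MMRM).

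Allocation and blinding states: "This is an open-label trial with no blinding implemented". According to the treatment section, both arms start filgotinib after the week-0 baseline assessment. The Add-on arm keeps MTX and the Switch arm does not.

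**The concern.** Randomisation protects a comparison only if membership of the analysed set does not depend on what happens after allocation. Here it depends on taking the first dose and on having an efficacy value.

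In a double-blind trial, dropping patients who were never dosed is usually harmless, because the decision not to start cannot depend on the arm. That defence is not available here. A patient or physician can learn the arm, consider whether MTX is to stop or continue, and decline. Enrolment may precede the start of treatment by up to 8 weeks. The interval between allocation and first dose is not stated.

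A patient who declines in this way disappears from every responder endpoint instead of counting as a non-achiever, and the numbers lost can differ between arms. No all-randomised analysis is described that would show whether this matters.

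**Working it through.** **1. Who is left out.** The table sets the FAS rule beside the non-responder rule and the MMRM.

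| Randomised patient | In the FAS? | Responder endpoints | Primary MMRM |
|---|---|---|---|
| Never takes filgotinib | No | Absent from numerator and denominator | Absent; would matter only if DAS28-CRP were measured after baseline |
| Takes filgotinib, no efficacy value after baseline | Yes if baseline counts; no if post-baseline is meant | Non-achiever, or absent | Adds no change score either way |
| Takes filgotinib, has a post-baseline value, then stops | Yes | Non-achiever | Contributes values up to stopping |

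The first row is certain, the second depends on an unstated word, and the third is handled properly already.

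**2. The stated sample size is not affected.** Inputs from Sample size calculation and Primary endpoint: margin 0.6, true difference 0.07, SD 1.1, one-sided 0.05, power 80%.

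n per group = 2 × [1.1 × (1.6449 + 0.8416) / (0.6 − 0.07)]² = 53.26, rounded up to 54. The total is 108, and 108 / 0.9 = 120. These are the article's figures, and the FAS wording does not enter them.

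**3. Responder endpoints.** Take 60 per arm from the article. Assume a responder rate p and k non-responders removed from one arm; the document gives neither. The rate moves from 60p/60 to 60p/(60 − k), a gain of p × k/(60 − k).

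| Assumed rate | k = 1 | k = 2 | k = 3 |
|---|---|---|---|
| 33/60 = 55.0% | 55.9% | 56.9% | 57.9% |
| 30/60 = 50.0% | 50.8% | 51.7% | 52.6% |
| 6/60 = 10.0% | 10.2% | 10.3% | 10.5% |

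The gain is 0.9 to 2.9 points at 55%, but at most 0.5 points at 10%. For CRRP and RRP the event is unfavourable, so removing patients without an event raises the rate and makes that arm look worse.

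**4. Primary endpoint, as an illustration.** Suppose k of 60 Switch patients and no Add-on patients are excluded, and their mean change is worse than the rest by g = 1.1 to 2.0 units (assumed). The estimated difference shifts towards Switch by s = (k/60) × g. If the all-randomised difference is exactly 0.6, the chance of declaring non-inferiority is Φ(s/SE − 1.645), with SE = 1.1 × √(1/60 + 1/(60 − k)). Without exclusions it is 5%.

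| k | Shift s | One-sided error |
|---|---|---|
| 1 | 0.02–0.03 | 6.0–7.0% |
| 2 | 0.04–0.07 | 7.2–9.4% |
| 3 | 0.06–0.10 | 8.5–12.4% |
| 6 | 0.11–0.20 | 13.3–25.0% |

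The last row is an extreme: it uses the whole dropout allowance of one arm (60 − 54 = 6). If similar patients leave both arms in equal number, the shift is about zero. If they leave Add-on only, it runs against Switch. Redefining the FAS removes such a shift only where the excluded patients have DAS28-CRP measured after baseline. A never-starter who withdraws will usually have none.

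**The case against.** The strongest reply is that this is an ordinary modified intention-to-treat set and that little follows from it. Four inferences that a reader might draw are indeed not supported.

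- **Early treatment failures leave the denominator.** A treated patient with a qualifying measurement stays in the FAS and counts as a non-achiever. Read literally, the baseline value may qualify, in which case almost no treated patient is lost. Even on the post-baseline reading, the Withdrawal criteria call for early-termination assessments, which narrows the loss. Never-starters are not treatment failures.
- **The FAS rule contradicts the non-responder rule.** Secondary endpoints names the FAS as denominator and then counts discontinuers within it as non-achievers. Statistical methods agrees. The passages are consistent.
- **The exclusions favour non-inferiority.** A patient may decline because MTX stops or because a new drug is added to it, so the direction is open. Non-inferiority is judged only on the MMRM difference, where a patient without post-baseline data adds nothing. The responder endpoints carry no non-inferiority test.
- **Every binary endpoint gains up to 2.9 points.** That figure rests on an assumed 55% rate, shrinks with lower rates, and reverses in meaning for CRRP and RRP.

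The Discussion also promises additional sensitivity analyses, although it names none on all randomised patients. These points limit the size of the problem. They do not answer its core: the article states a rule that lets allocation-dependent non-starters leave the responder endpoints. That is a rule fixed in the text, not a detail left to a fuller document.

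**Conclusion.** The point holds in limited form and should be corrected. The arms are not compared as randomised in any efficacy analysis described, and knowledge of the arm can influence who starts. The certain effect is on never-starters in the responder endpoints. The effect on treated patients without follow-up depends on what the measurable point means.

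The size cannot be computed from the document, which gives no rate of non-starters. One to three one-sided exclusions of non-responders would move a responder rate by about 1 to 3 points at a rate near 55%, and by less at lower rates. The effect of the definition on the primary MMRM is small. The larger shifts in the illustration need one-sided loss of patients with clearly worse outcomes, and the definition alone would not recover outcomes that were never measured. No stated figure is wrong.

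**What to change.** Before data lock:

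- Define the FAS as all randomised patients, analysed in the arm allocated.
- Use it as the denominator for the favourable responder endpoints, with patients lacking data counted as non-responders.
- Fit the primary MMRM to all randomised patients with DAS28-CRP data.
- Keep the present definition as a supplementary set, say whether its measurable point must be post-baseline, and report by arm how many randomised patients fall outside it and why.
- For CRRP and RRP, do not carry over the non-responder rule as if it were conservative. Counting a missing radiograph as no progression lowers the event rate, so these endpoints need their own stated rule.

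This costs a few sentences and needs no extra patients or visits. The planned 120 is unchanged. The one downside is that reported responder rates may be slightly lower.

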#### Per protocol set (PPS).

Among the FAS, subjects without any major protocol deviations will be included in the PPS as the population for sensitivity analysis of efficacy. The handling of major protocol deviations and cases will be determined through consultation between the lead investigator, data center, and statistical analysis team before finalizing the study data. In clinical trials, adherence rates for once-daily investigational drugs have generally been reported to be in the 70% range [17]. In our study, we adopted a slightly stricter criterion, defining non-adherence as an adherence rate of less than 80%. If the adherence rate to the study drug is less than 80% up to week 24, the subject will be excluded from the PPS analysis.

### Statistical methods

For the primary endpoint, the change in DAS28-CRP from baseline will be analyzed using a Mixed Effects Model for Repeated Measures (MMRM). This method considers the baseline measurement as a covariate and incorporates group, time point, and the interaction between time point and group as fixed effects. It also reflects the variance-covariance structure of repeated measurements within each patient. Using this model, the least squares mean difference between groups at week 24 and its 90% confidence interval will be calculated. Non-inferiority will be confirmed if the upper limit of this 90% confidence interval is less than 0.6.

For the secondary endpoints, the proportion of patients meeting each endpoint and the corresponding 95% confidence intervals will be calculated. For the change from baseline in each endpoint, summary statistics (number of patients, mean, standard deviation, minimum, median, and maximum) will be presented. Additionally, the change from baseline will be analyzed using the same MMRM approach as for the primary endpoint, estimating the least squares mean and its 95% confidence interval at each time point.

As a sensitivity analysis, stratification will be performed based on stratification variables (history of bDMARD use and anti-CCP antibody positivity/negativity), and summary statistics will be calculated for baseline values, measurements at each time point, and changes from baseline by treatment group and treatment period, with intergroup comparisons conducted using t-tests.

Additionally, as a supplementary analysis, in the PPS population, intergroup comparisons of changes from baseline will be conducted using MMRM, and summary statistics will be calculated with intergroup comparisons performed using t-tests. Furthermore, in the PPS population, stratification based on the aforementioned stratification variables will be conducted, and summary statistics will be calculated for baseline values, measurements at each time point, and changes from baseline by treatment group and treatment period, with intergroup comparisons conducted using t-tests.

For the cumulative values of CRP and MMP-3, the AUC for each participant will be calculated, and summary statistics (number of patients, mean, standard deviation, minimum, median, and maximum) for each group will be presented.

For the safety analysis, treatment-emergent adverse events (TEAEs) observed during the period from the start of the study treatment to the end of the observation period will be summarized. Adverse events that cannot be ruled out as being causally related to the study treatment will be classified as adverse drug reactions. For each group, the number and percentage of cases of TEAEs and adverse drug reactions will be summarized by system organ class and preferred term. Additionally, a summary by severity level will also be provided.

Missing data at each time point will not be imputed. For patients who discontinue the study, only the data obtained up to the point of discontinuation will be used for analysis. Additionally, when analyzing the proportion of patients who achieve the endpoint, cases with missing data at each time point, including those who discontinued the study, will be considered as non-responders and included in the denominator.

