### Sample size calculation

Based on the results from the DARWIN1, DARWIN2, and FINCH3 trials, this study assumes a mean difference in change from baseline in DAS28-CRP at week 24 between the two groups of 0.07, with a standard deviation of 1.1. With an equal sample size ratio of 1:1 between the groups, and assuming a mean difference of 0.07, a standard deviation of 1.1, a one-sided significance level of 0.05, and a power of 80%, the required sample size was calculated to be 108 participants (54 per group). As for the sample size calculation, a one-sided test was employed based on the clinical assumption that filgotinib monotherapy would not be inferior to the combination of filgotinib and MTX. Considering a dropout rate of approximately 10%, the total sample size was set at 120 participants (60 per group).

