The study protocol defines multiple efficacy endpoints, including DAS28-CRP changes, ACR response rates, quality-of-life measures such as HAQ and WPAI, and radiological changes, indicating a comprehensive endpoint design. Safety endpoints are also robust, emphasizing AEs and laboratory abnormalities. Furthermore, allowing shared decision-making between patients and rheumatologists post-week 24 reflects a patient-centric approach, providing flexibility in tapering or restarting MTX based on clinical need. On the other hand, the limitation of this study is the lack of blinding which may introduce bias in subjective endpoints like patient-reported outcomes. However, this open-label design allows for a more practical evaluation of treatment effectiveness in a real-world setting, where patients and physicians are aware of the treatments being administered, potentially enhancing adherence and capturing a broader range of patient experiences.

In clinical trials, outcome measures are often repeatedly assessed in the same individuals over time, resulting in longitudinal data. However, it is common for participants to discontinue the study or miss scheduled visits, leading to incomplete or missing data. MMRM is a likelihood-based approach that provides valid estimates under the assumption of missing at random (MAR), without requiring data imputation. MMRM utilizes available data while accounting for baseline covariates and within-subject correlations, making it a robust method when the mean and covariance structures are correctly specified. However, as the missing data mechanism cannot be directly verified from observed data, and MMRM is only valid under MAR, it is important to consider alternative analytical approaches when its assumptions are not met. In this study, we acknowledge these limitations and will explore additional sensitivity analyses to ensure the robustness of our findings.

In conclusion, the FAITHFUL study protocol is well-designed to address an important clinical question in the management of rheumatoid arthritis. By leveraging a randomized, multicenter approach, the study could provide pivotal evidence on the viability of filgotinib monotherapy as an effective alternative for MTX-refractory patients.

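### Minor, cheap improvement: the primary MMRM has no baseline-by-time-point term, so one baseline slope serves every visit and the week-24 contrast may be imperfectly adjusted

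*Protocol article*

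**What the plan says.** The Statistical methods section of the protocol article gives the mean structure of the primary model: "baseline measurement as a covariate and incorporates group, time point, and the interaction between time point and group as fixed effects". On covariance it adds only this: "It also reflects the variance-covariance structure of repeated measurements within each patient". From the model, "the least squares mean difference between groups at week 24 and its 90% confidence interval will be calculated", and the decision rule is: "Non-inferiority will be confirmed if the upper limit of this 90% confidence interval is less than 0.6". Secondary change-from-baseline endpoints use the same MMRM approach. No baseline-by-time-point term is listed.

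Three other places bear on this. Allocation and blinding names two minimisation factors, prior bDMARD use and anti-CCP status; baseline DAS28-CRP is not one of them. Sample size calculation proceeds by "assuming a mean difference of 0.07, a standard deviation of 1.1" and states no reduction for baseline adjustment. The Discussion describes MMRM as using baseline covariates and within-subject correlation, "making it a robust method when the mean and covariance structures are correctly specified".

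**The concern.** The response is change from baseline. At visit t its slope on baseline is corr(t) × SD(t)/SD(0) − 1, where corr(t) is the correlation between the baseline value and the value at visit t. A single slope is exact only if corr(t) × SD(t) is the same at every visit. Here every patient starts filgotinib, other DMARDs stop at that point, and MTX stops in one arm. It is therefore plausible, though not documented, that week 4 tracks baseline more closely than week 24 does. The common slope would then be flatter than the true week-24 slope.

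Two things would follow at week 24. Part of any chance baseline difference between the arms would stay in the estimate compared with 0.6, and the residual variance would be larger than it needs to be. Because minimisation does not balance baseline DAS28-CRP, only randomisation and this covariate deal with it. Planned power leaves little slack.

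**Working it through.** **The plan's own figure.** Inputs from Sample size calculation and Primary endpoint: margin 0.6, true difference 0.07, SD 1.1, one-sided alpha 0.05, power 80%, 1:1 allocation.

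n per arm = 2 × 1.1² × (1.645 + 0.842)² / (0.6 − 0.07)² = 53.3, rounded up to 54, so 108 in total, and 108/0.9 = 120. The stated size reproduces. At 54 per arm, power is 80.5% and the 90% CI half-width is 1.645 × 1.1 × √(2/54) = 0.348.

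**Formulas for the common-slope model** (large sample, complete data, unstructured covariance). Let β_t be the visit-specific slopes and S the residual covariance given baseline.
- Common slope: b = 1′S⁻¹β / 1′S⁻¹1.
- Variance of the week-24 contrast relative to visit-specific slopes: 1 + Var(baseline) × (β₂₄ − b)² / S₂₄.
- Shift left unadjusted per 1-SE baseline imbalance: (β₂₄ − b) × SD(baseline) × √(2/54).

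**Assumptions, none of which the article gives.** Follow-up SD 1.1 at every visit; baseline SD 0.9 (an SD of 1.1 gives the same variance ratio and shift, because baseline SD cancels when the follow-up SD is constant); residual correlation falling with visit distance, adjacent value 0.5 to 0.7; three or four visits to week 24, since the full visit list is in a figure that is not shown.

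**One case in full** (correlations 0.60/0.45/0.35, residual correlation 0.5). Slopes are 0.60 × 1.1/0.9 − 1 = −0.267, then −0.450 and −0.572. The weights are 0.52, 0.16 and 0.32, so b = −0.395 and β₂₄ − b = −0.177. S₂₄ = 1.21 × (1 − 0.35²) = 1.062. The variance ratio is 1 + 0.81 × 0.177²/1.062 = 1.024, so the CI is √1.024 − 1 = 1.2% wider. The shift is 0.177 × 0.9 × √(2/54) = 0.031.

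| Correlations with baseline up to week 24 | Week-24 variance | 90% CI width | Shift per 1-SE imbalance |
|---|---|---|---|
| Flat: 0.40/0.40/0.40 | 0% | 0% | 0 |
| Mild: 0.50/0.40/0.35 | +0.7 to 0.8% | +0.3 to 0.4% | 0.016–0.018 |
| Mild: 0.60/0.55/0.50/0.45 | +0.9% | +0.4 to 0.5% | 0.017–0.018 |
| Moderate: 0.60/0.45/0.35 | +2.4 to 3.0% | +1.2 to 1.5% | 0.031–0.034 |
| Moderate: 0.70/0.60/0.50/0.40 | +4.1 to 4.9% | +2.0 to 2.4% | 0.039–0.043 |
| Steep: 0.75/0.60/0.50/0.35 | +8.0 to 10.1% | +3.9 to 4.9% | 0.056–0.063 |
| Steep: 0.70/0.45/0.25 | +9.9 to 13.2% | +4.8 to 6.4% | 0.065–0.075 |
| Rising: 0.30/0.35/0.45 | +0.6 to 0.7% | +0.3% | 0.014–0.016, over-adjusted |

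In patients, 108 − 108/1.02 and 108 − 108/1.05 give about 2 to 5 of 108 for a moderate fall; 108 − 108/1.08 and 108 − 108/1.13 give about 8 to 12 for a steep one. With six visits to week 48 in the model, the widening is smaller: 0.5–0.7% for a moderate and 2.7–3.7% for a steep fall.

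**Simulation** (4,000 trials per scenario, 54 per arm, weeks 4/12/24, complete data, true difference 0.07).

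| Scenario | SE ratio, common slope / interaction | Power, common slope | Power, interaction |
|---|---|---|---|
| Flat | 0.995 | 87.5% | 87.1% |
| Moderate (0.60/0.45/0.35) | 1.008 | 83.5% | 83.9% |
| Steep (0.70/0.45/0.25) | 1.049 | 78.6% | 82.3% |

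One-sided error at the margin was 4.8–5.4% for both models, and mean estimates were 0.063–0.070. The common-slope estimate moved with baseline imbalance (regression slope −0.14 for moderate, −0.35 for steep); the interaction model's did not (0.02 and 0.00).

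**The case against.** The strongest reply is that nothing here is wrong. A common-slope MMRM is a valid specification, its error rate at the margin holds, and with complete data it is unbiased on average. All of that stands. It also stands that the loss depends on correlations the article does not give, that with equal slopes the simpler model had the smaller standard error in about 95% of simulated trials, and that the sizing is largely unaffected. In the flat, mild and moderate cases the common-slope half-width (0.31–0.33) is below the 0.348 implied by the planning SD. It exceeds that figure only in the 0.70/0.45/0.25 case (0.353–0.359, against 0.337 with the interaction).

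It can also be said that the article condenses a fuller document and that the SAP may contain the term. This carries less weight. The article does not leave the mean structure open; it lists it. A SAP with the interaction would depart from the published list, so the two should be aligned.

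A reader might infer more than the documents support:
- **That the week-24 contrast is under-adjusted and its interval too wide.** This is conditional. With flat correlations there is no loss, and with rising ones the contrast is over-adjusted.
- **That the Discussion concedes misspecification.** Its sentence is a general remark on MMRM with missing data, and the same paragraph says further sensitivity analyses will be explored.
- **That visits after week 24, when MTX may be changed, distort the primary slope.** Statistical methods does not say that those visits enter the primary model.

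The absence of bias is shown only for complete data. In a further simulation (60 per arm, about 10% dropout after the first visit, baseline-related dropout in the Switch arm, 600 trials), the common-slope estimate exceeded the interaction model's by 0.02 to 0.04 under moderate to steep falls. With the same dropout in the Add-on arm the sign would reverse. That pattern is assumed, and the shift is small against 0.6.

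**Conclusion.** The point holds as a minor improvement. The stated model implies one baseline slope for all visits. If the true slopes differ, the week-24 difference may carry part of a chance baseline imbalance, up to about 0.07 DAS28 units per 1-SE imbalance in the steepest case examined. The variance cost under the assumed correlations is 0% (flat), about 1% (mild), 2–5% (moderate) and 8–13% (steep). Only a steep fall costs noticeable power, between 3 and 4 points in the simulation. The validity of the non-inferiority test is not in question. These sizes rest on an unstructured covariance, complete data, a constant follow-up SD and visits up to week 24; other covariance structures were not examined. The case for change is the asymmetry: the possible loss from omitting the term exceeds the known cost of including it.

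**What to change.** Before outcome data are seen, add the baseline DAS28-CRP by time-point interaction to the primary MMRM in Statistical methods, and state the same model in the SAP. Use the same form, with each endpoint's own baseline, for the secondary change endpoints analysed by MMRM. Margin, confidence level and sample size stay as they are.

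The cost is one model term and no new data. It uses one degree of freedom for each post-baseline visit beyond the first (two with three visits, three with four), out of roughly 100. If the slopes are in fact equal, the standard error is about 0.5% larger and simulated power 87.1% instead of 87.5%. Restricting the primary model to visits up to week 24 is optional and is not needed for this point.
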